## Abstract

**Background:**

This study looks at the effect of immediate session-by-session feedback using short questionnaires for evaluating outcome of and alliance in the therapy. Research data strongly suggests that using this feedback informed treatment improves the outcome of therapy. However, until now, this method of Miller and Duncan has only been examined in clients (generally students) with mild problems and in partner counselling. The question addressed by this study is whether immediate feedback is also effective when applied during crisis intervention and subsequent brief therapy in a psychiatric patient population in emergency situations. It also looks at whether 'feedback-informed treatment' affects the quality of the alliance.

**Method/Design:**

To test the hypotheses, all patients seeking help from the Crisis Intervention & Brief Therapy Team over a two-year period will be followed throughout their treatment up to a maximum of six months and a follow-up period of three months after ending the treatment. Patients are randomly assigned to two conditions: treatment without feedback and treatment with immediate feedback for each session. The therapists all operate in both conditions and so they deliver both treatments. An estimated total of 180 patients, aged 18 years and over, will be included in the study.

**Discussion:**

The aim of this study is to make clear whether, and to what extent, systematic feedback from the patient in this target group during therapy determines the course and outcomes of therapy. We also look at whether, and to what extent, the quality of the alliance and the motivation of the person delivering treatment with respect to the instruments play a role.

**Trial registration:**

NTR3168

## Background

Principal research showed, in a range of meta-analyses, that all bona fide psychotherapy treatments are, in broad terms, equally effective [1-7]. This finding, combined with economic concerns, led to a search for methods to improve treatment outcomes in other ways than the traditional evidence-based research. Out of this search, a new paradigm for evaluating psychotherapy came forward, introduced by Howard [8]: *patient focused research*. Central in this type of research is monitoring, modelling and predicting individual treatment progress and providing feedback about this information to therapists (and patients) during the course of treatment [8-10]. In this 'feedback-informed treatment' [11], therapists are supposed to identify patients at risk of treatment failure in an early phase and to make changes to their approach when necessary [9,12-16].

### Patients at risk of failure

When patients benefit from therapy, this generally happens in an early phase of treatment [17,18]. Several authors have looked at the issue of whether 'early symptom change', as experienced by the patient, is a feasible predictor of a good outcome in given patient-therapist combinations [9,15,19,20]. Lambert [9] found that in 84% of early changers subsequent therapy was positive; approximately 25% of the clients actually underwent a dramatically rapid improvement that –usually- led to sustained recovery. Howard et al. [14] found not only that change occurred earlier rather than later in the course of treatment, but also that the absence of early change diminished the probability of symptom reduction and improved well-being at the end of treatment. Brown et al. [12] found that when there is no improvement after three sessions generally no improvement will be achieved over the entire course of treatment; they also found that patients who report deterioration by the third session have a drop-out risk twice as high as patients who report improvement. An improvement in well-being in the first 3–5 sessions therefore has predictive value for the course of therapy. Also more specific patterns of early change, slow and fast have been identified [21].

### Results of feedback

In the first studies, feedback about symptom change was only given to the therapist. In a meta-analysis of three studies Lambert et al. [22] concluded that adding feedback to a treatment led to better outcomes, reporting an average Effect Size (ES) of 0.39.

Later, different forms of feedback have been developed providing both therapist and client with information. A meta-analysis of five studies [9] also reported a positive effect: fewer patients deteriorated in the feedback condition – 20% as opposed to 12% – and that more patients improved (defined as achieving clinically significant change) - 22% versus 45%-.

Several studies have been performed to establish which form of feedback offers the best results. Most feedback research is focused on the early identification of patients who are 'not on track' or whose scores develop in ways that differ from the expected scores in a negative way [9,14,16,23].

A comparison of several forms of feedback was made by Knaup [24] in a meta-analysis, including a total of twelve studies. Here also, the effect - at least in the short-term- on health outcomes proved to be significant in all feedback studies. However, the average effect size was lower (0.10) than in the earlier meta-analyses, and the effect could not be demonstrated during follow-up measurement. An important finding was that feedback was more effective when information about (lack of) patient progress was supplied, feedback was given frequently (more than twice) and given to both patient and therapist. It can also be concluded from this meta-analysis that the main effect of feedback results from identifying the Not On Track group in time [25].

### Feedback instruments

The feedback studies that meet the requirements that can be derived from the findings of Knaup as mentioned above, are the studies using the Outcome Questionnaire 45 (OQ45) of Lambert and the Partners for Change Outcome Management System (PCOMS) of Miller and Duncan [26,27]).

In the most recent meta-analysis, Lambert & Shimokawa [28] performed a meta-analysis of the effects of both the OQ45 and PCOMS, including a total of 9 randomized controlled trials. This study comprises six randomized studies on the OQ45 and three randomized studies on PCOMS. The latter concerning individual therapy in a student counselling university setting [29], and couples therapy in the context of an (American) university therapy training programme [30], respectively a (Norwegian) family counselling agency [31].

Lambert & Shimokawa found effects sizes varying from .23 to .33. They concluded that the number of psychotherapy patients who deteriorate (5–10% in adult therapy, 14–24% in child psychotherapy, in routine care) can be cut in half by use of these systems. Here also, the main effect comes from identifying Not On Track clients in good time. However, in some of the studies analyzed also beneficial effects were reported for ‘On Track’ clients [31-33].

### Limitations of studies: differences in setting and instruments

However, a limitation of these studies is that they are performed in psychotherapeutic settings and in populations with only mild distress and not suffering from psychiatric disorders. De Jong recently performed two feedback studies with the OQ45 in a naturalistic setting including patients with various psychiatric disorders. In the first study [34], for the full sample no beneficial effect of feedback was found and there was no effect of feedback on patients being Not On Track (NOT) either. In NOT cases a positive significant effect was found only when therapists indicated that they actually used the feedback. Feedback in this study however was only given to the therapist and not to the client, and not on a session-by-session basis.

In the second study [35], immediate feedback to only therapists was compared to feedback to both therapist and patient (vis-à-vis a non-feedback condition). Though feedback was applied each session, no overall effect was found either. However, applying feedback appeared to be preventive of negative change for NOT cases in short-term therapies (d = 1.28 after 35 weeks) but this effect was not strong enough to bend the course of treatment in the direction of positive change. Feedback was most effective when applied to both client and therapist. The findings that feedback was most effective for clients who were Not On Track and when feedback is supplied to both client and therapist, match with the conclusions of Lambert [9] and Knaup [24]. However, the study of De Jong was performed in a population with only mild distress (mean base line OQ45 69.2 resp. 74,6), comparable to Lamberts studies (mean OQ45 68–78), excluding patients in crisis and patients with a psychotic disorder.

Another limitation of all the studies mentioned is that the applied feedback measure was identical to the outcome measure; there was no use of an additional outcome measure independent of the feedback instrument.

Taking into account this state of affairs, it is still an open question whether feedback instruments should be implemented in daily psychiatric practice. Further studies should be conducted in a psychiatric population focusing on clients in severe distress, and using outcome measures that are not identical to the feedback measures. Such a study is provided for in this design.

### The role of the alliance

Repeatedly, the literature has shown that the therapeutic alliance is an important factor in psychotherapy [36]. There is some evidence that various measures of early (relationship-related) interpersonal in-session processes account for at least 8% to 14% of explained outcome variance [36,37].

Patient ratings of the therapeutic relationship between Sessions 3 and 5 provide reasonable predictions of treatment outcome [38]and a low score for the quality of the alliance emerged as a predictor for premature termination of treatment [39,40].

Though change and alliance are mutually connected and hard to separate, analyses have been performed to try to disentangle this relation [41-43], indicating that both phenomena have separate influences on outcome. So, apart from ‘early change’, the alliance has emerged from patient-focused research as a second predictor of outcome.

There are indications that timely detection of a poor working alliance results in better outcomes and that feedback about this topic can initiate improvement/remediation of the relationship, preventing stagnation in the therapeutic process and identifying potential drop-out in good time [31,42,44].

### Results of studies on alliance on feedback

Scarce studies have been performed on the specific effect of feedback on alliance in relation to outcome (Whipple [16], Harmon [38] and Slade et al. [45], Crits Christoph [37]). Fluckiger et al. (2013) [46] found that multiple interconnected components simultaneously influence the early phase of treatment, while interpersonal distress at intake as well as the early interpersonal session experiences by patients and therapists seem to be robust predictors of outcome. These findings underscore that therapists need to monitor and discuss intra- as well as interpersonal experiences early in therapy, though its interaction is not yet fully understood.

It is yet unclear whether feedback on the alliance improves alliance, and it is equally unclear whether feedback on the alliance actually boosts outcome; let alone if these mechanisms work similar in a psychiatric and psychotherapeutic settings. Subsequently, it is unknown if applying an alliance measure to a feedback system (like in PCOMS) actually contributes to the improvement of outcome.

These considerations taken into account, it is important that a future study on feedback informed treatment adds a separate instrument for measuring the quality of the alliance in both feedback and non-feedback condition. Hence making it possible in a more independent way to examine if feedback (on alliance) actually influences the quality of the alliance; and to examine the relation between separately measured alliance scores, alliance scores provided by the feedback instrument and outcome scores.

The design of this study meets this requirement by adding the Helping Alliance Questionnaire II for both client and therapist.

In summary, we can conclude the following from the studies above.

Immediate feedback would appear to be a promising method but, at the outset of our study, studies were restricted to a few specific populations such as students and partner counselling, with the level of distress at the outset of the treatment appearing to be relatively limited (with an average ORS score of about 20). The method has not yet been studied in patients with severe and acute psychiatric symptoms.

Also, it is yet unclear if feedback on alliance improves the alliance and if this process influences outcome. In feedback studies, both outcome and alliance have not yet been examined with independent measures so far.

Taking into account all considerations mentioned before, the research questions for this study are:

1) to examine whether applying immediate feedback at each treatment session in a psychiatric population with severe distress results in better outcomes (10% fewer complaints, enhanced well-being), higher client satisfaction and a more efficient treatment (shorter treatment duration) compared with the no-feedback condition (the same therapists operating in both conditions). Outcome has to be measured with a measure independent from the instrument used in the feedback process.

2) to examine whether applying immediate feedback at each treatment session results in improvements to the alliance; and whether there is a link between any improvement in alliance and improvement in treatment outcome. Alliance to be measured with a measure independent from the instrument to be used for feedback.

## Methods

### Design

The study is a randomised controlled trial covering all patients presenting to the Crisis Intervention & Brief Therapy team over a period of two years (starting October 2009). When patients are presented to the CI&BT team, they are randomised to the experimental condition (EXP) or the control condition (TAU). The EXP condition uses an immediate feedback method for each treatment session; the TAU group does not use formalized feedback.

### Experimental intervention

The experimental condition receives treatment using the immediate continuous feedback method Partners for Change Outcome Measurement System (PCOMS).].

The therapist establishes in dialogue with the client how scores should be interpreted and how to optimize the chances of progression during the therapy sessions coming.

In the EXP condition, clients complete the ORS (‘How are you doing?’)with a member of the research staff preceding every session. The results are presented in a graph, together with the ORS scores of the previous contacts. A printed version of this graph is given to the clients, who then discuss it with their therapist. At the end of the session, the therapist asks the patient to complete the SRS ( ‘How did you experienced the meeting?’); once this has been done, the resulting feedback is discussed on the spot. The SRS is, once it has been discussed with the therapist, passed onto the researcher after the end of the session. In both conditions, patients are treated by the same therapists using the same therapeutic method and systemic crisis intervention; supplemented by the CDOI feedback method for patients in the experimental condition.

### TAU condition: treatment as usual

The treatment delivered to both the TAU and the EXP groups can be described as crisis intervention in combination with brief therapy. The approach is an integrative model in which both psychiatric treatment and systemic therapy approach play an important role. This treatment method has been described extensively in the Dutch Crisis Intervention Practice Handbook [47]. At present, there are no comparable crisis intervention treatment models that are known to have been scientifically studied [48]. The approach to treatment used is ‘practice-based’ too. The TAU for crisis cases is delivered, as in the EXP condition, by the staff of the CB&BT team of the Amsterdam mental health organisation Mentrum (part of a the Arkin institute). This team has extensive experience with helping people in crisis situations. The organisation of the team resembles that of Assertive Community Treatment teams: intensive outreach care, partial sharing of caseloads, working in co-therapy and immediate availability. Since the target group consists of patients suffering from a variety of symptoms, the therapeutic approach also covers a broad range of interventions. The content of the method applied includes elements from family-therapy, picking up on strengths and individual responsibilities in the system, and elements from the solution-driven approach. The attitude places a strong emphasis on motivational techniques.

Clients undergo standard psychiatric examination, supportive and structuring interventions and systemic interventions. Psycho-education, pharmacotherapy, a monitoring plan, change-oriented interventions or admission to a clinic are treatment options on offer.

Treatment is delivered in the community as much as possible. The basic philosophy of the CB&BT team involves supplying 'system-oriented tailored care': the optimal combination and intensity of interventions is established for each client system. These can vary during the course of the treatment. Treatment continuity is a goal; treatment is delivered as much as possible by the same two therapists. The therapists come from different disciplines: doctors (residents), psychiatrists, psychologists and psychiatric nurses. The core team consists of experienced therapists. The team is supplemented by a group of residents that changes every six months. The primary focus of the treatment is to help clients regain a sense of mastery over their lives again. However, compulsory admissions also take place when necessary if clients are unfit to make their own decisions and their behaviour is dangerous.

Therapists can ask for consultation about difficult cases any moment. A consulting psychiatrist is always available, and daily case meetings are open to any therapist who faces a problem or feels a case is not progressing. This means there is no principal difference in the quality and availability of services between TAU and Experimental Intervention.

### Randomisation

When entering the treatment facility, patients will be randomly assigned to one of both conditions. Randomisation is performed by a member of the research team before contact with the therapist takes place. There is no assessment for eligibility, all patients referred to the CI&BT team will be included in the study. Though, after the first or second assessment session, a substantial part of the clients is being referred to other services, for instance send to their GP or admitted to a hospital. Only a limited group of clients will be indicated to continue treatment at the CI&BT team. Those who continue treatment after two assessment sessions form the group that is subject to this study. At first contact it is not clear whether a client will be referred to other services or taken into treatment at the CI&BT team, while treatment has already started the moment this becomes clear. As a consequence, only after two sessions it is evident which patients will participate in the definite research condition.

So, a substantial group of randomised patients will be excluded. This post-randomisation exclusion is inevitable, given the nature of the service. Excluding patients from an analysis does not necessarily bias the results, provided that certain requirements are met, for instance that intention-to-treat applies to all randomised patients [49]. Baseline characteristics of all patients, such as gender, ethnicity, education, marital status, diagnosis and level of functioning, shall be analysed to make sure selective exclusion does not bias the results.

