#### Procedures and time points

Initial assessment (the 'baseline measurement') takes place when patients first come into contact with the Crisis Intervention & Brief Therapy Team. The intervention lasts a maximum of six months and stops when treatment ends or after six months.

The PCOMS questionnaires are completed and discussed at every session in the EXP condition. In the TAU condition, every six weeks the ORS form is completed and handed over to a research assistant, without discussing it with the therapist. In both conditions, starting at the time of the baseline measurement, additional questionnaires (BSI, HAQII) are completed by patients in both conditions after 6 weeks, 12 weeks, 18 weeks and 24 weeks of treatment. The therapist also completes questionnaires at the same point in time (6, 12, 18 and 24 weeks after treatment starts) about the course of treatment (CGI) and the alliance (HAQII). When treatment ends, all questionnaires are being completed once again. The follow-up measurement takes place three months after the end of treatment.

Before the study starts, the therapists are required to complete a one-off questionnaire measuring their attitude to the instrument and their motivation with respect to the use of feedback in general. The same questionnaire will be completed by the therapists after the study period.

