### Data analysis

#### Sample size calculation

With two groups of 90 patients, an alpha of 0.05 (one-tailed), an effect size of about 0.3 on the Global Severity Index at 12 weeks (mean EXP group = 1.0; mean TAU = 1.3; standard deviation at week 12 is 0.80) can be detected with a statistical power of 80%. Analysis will be performed according to the intention to treat principle.

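### The analysis is called intention to treat, but patients who do not continue past two sessions are excluded after randomisation and after feedback has begun

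*Protocol article*

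**What the plan says.** All references are to the protocol article.

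- **Who is randomised and when** (Randomisation): "There is no assessment for eligibility, all patients referred to the CI&BT team will be included in the study". "Randomisation is performed by a member of the research team before contact with the therapist takes place".
- **Who is analysed** (Randomisation): "Those who continue treatment after two assessment sessions form the group that is subject to this study". The consequence is stated openly: "So, a substantial group of randomised patients will be excluded". No proportion is given. The examples of leaving are referral to the GP and hospital admission.
- **What has happened by then** (Randomisation): whether a patient will stay is not known at first contact, "while treatment has already started the moment this becomes clear". Under Procedures and time points: "The PCOMS questionnaires are completed and discussed at every session in the EXP condition". The Experimental intervention section places the ORS before every session and the SRS at its end. The control arm (TAU) completes the ORS every six weeks, without discussion with the therapist.
- **What the analysis is called** (Sample size calculation): "Analysis will be performed according to the intention to treat principle".
- **The defence offered** (Randomisation): exclusions need not bias results, "provided that certain requirements are met, for instance that intention-to-treat applies to all randomised patients". Baseline characteristics of all patients will also be analysed, as an assurance that selective exclusion has not biased the results.

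**The concern.** Intention to treat protects a comparison because the groups analysed are the groups that chance created. Here the groups are fixed later, by who continues after two sessions, and in those sessions only one arm discussed feedback. If feedback affects who continues, continuers in EXP and TAU can differ for reasons other than the effect of feedback on outcome.

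The article itself makes such an influence plausible. Patients at risk of failure, The role of the alliance and PCOMS tie early change and alliance to drop-out. Session rating scale describes a check, as part of the SRS discussion, that the client is confident enough to return. Interpretation and consequences of the ORS and SRS scores has therapists compare progress with expected curves and treats a lack of improvement in the initial sessions as a predictor of failure and drop-out.

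At stake is what the primary comparison can claim. A reader who sees the intention-to-treat label will credit the result with the full protection of randomisation, which this set does not have.

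**Working it through.** **1. The statements side by side**

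| Element | Article | Consequence |
|---|---|---|
| Randomised | All referred patients, before therapist contact | Full intention-to-treat set = all referred |
| Analysed | Those continuing after two sessions | A subset defined after randomisation |
| Exposure before the subset is fixed | PCOMS at every EXP session; treatment already started | Subset defined after exposure |
| Label | Intention to treat | Does not describe the subset |
| Condition for harmless exclusion | Intention to treat on all randomised | Not met, because of the exclusion |

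One mild ambiguity: the first two contacts are called assessment sessions, and the Design section ties feedback to treatment sessions. Experimental intervention and Procedures and time points say every session, without exempting the first two, and Randomisation says treatment has begun. The natural reading is that feedback has started.

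**2. The plan's own figure**

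Inputs (Sample size calculation): 90 per group, means 1.0 and 1.3, SD 0.80, one-sided alpha 0.05.

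- Standard error = 0.80 × √(2/90) = 0.119.
- Power = Φ(0.3/0.119 − 1.645) = 80.8%, against 80% stated.

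The figure reproduces, so the point does not rest on an arithmetic error.

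**3. How selection could act (illustration only)**

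Assumptions not in the article: no true effect; patients continue if a latent severity trait exceeds a cut-off; the trait has correlation ρ with week-12 GSI; SD stays at 0.80; 90 analysed per arm. If a share p continues, the mean GSI of continuers shifts by ρ × 0.80 × λ(p), with λ(p) = φ(z)/p and z the normal cut-off leaving a share p above it.

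λ(0.40) = 0.966, λ(0.45) = 0.880, λ(0.50) = 0.798, λ(0.55) = 0.720, λ(0.60) = 0.644.

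Spurious difference = ρ × 0.80 × [difference in λ], in GSI points:

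| TAU / EXP continuing | Difference in λ | ρ = 0.3 | ρ = 0.5 | Direction if the more severe continue |
|---|---|---|---|---|
| 50% / 50% | 0 | 0 | 0 | none |
| 50% / 60% | 0.154 | 0.037 | 0.062 | favours EXP |
| 50% / 40% | 0.168 | 0.040 | 0.067 | against EXP |
| 55% / 45% | 0.160 | 0.038 | 0.064 | against EXP |
| 60% / 40% | 0.322 | 0.077 | 0.129 | against EXP |

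In the 50% / 60% case the one-sided type I error is 1 − Φ(1.645 − shift/0.119), which is 9.1% (ρ = 0.3) to 13.0% (ρ = 0.5) instead of 5%. Every direction reverses if the less severe continue.

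**4. The planned analysis is relative to baseline**

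The Primary analysis section compares each follow-up with baseline; the table uses the raw week-12 mean. If the trait is stable and has the same ρ and SD at baseline, the shift at baseline is also ρ × 0.80 × λ(p), and the shift in the change is

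ρ × 0.80 × λ(p) − ρ × 0.80 × λ(p) = 0.

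Bias then remains only where selection acts on early response or on factors that baseline GSI does not reflect. The table may therefore overstate what would reach the primary comparison.

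**5. What a baseline comparison can show**

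It can reveal imbalance in the listed characteristics. It cannot show selection on response during the two sessions, which comes after baseline, or on unmeasured factors. These are the routes that survive step 4.

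**The case against.** The strongest defence is that nothing is hidden. The article discloses the exclusion, explains why a crisis service cannot know at entry who will stay, and plans a baseline check on all patients. Its research question concerns feedback during treatment, so patients referred elsewhere after one or two contacts are arguably not the population of interest. That justifies studying continuers. It does not justify the intention-to-treat label, or the claim that a baseline comparison gives assurance.

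Stronger readings are tempting, and these parts of the defence stand:

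- A reader might infer that unblinded therapists, having seen EXP scores, decide who stays. The article names no decision-maker, and it describes consulting psychiatrists and daily case meetings. Therapist influence is plausible, not stated.
- A reader might infer that patients who fail to return are excluded too. Only referral and admission are given as examples; whether non-return counts is not stated.
- A reader might express the illustrative shifts as a share of the planned effect and take that as the size of the bias. The retention gaps and correlations are assumed, the sign can go either way, and the shift may shrink or cancel relative to baseline.
- A reader might conclude that randomisation should move to after the second session. Inclusion was to run for two years from October 2009, and the article reports the 2009–2011 diagnoses as past, so recruitment appears closed. The move would also take feedback out of the first sessions, within the early phase the article regards as predictive.

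Detailed sensitivity analyses are commonly left to an analysis plan. Their absence is not the finding; the label, the defence and the assurance are, because the article itself fixes them.

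**Conclusion.** The point holds as a contradiction within the article. The analysed set is a post-randomisation subset, fixed after discussed feedback has begun in one arm. It is called intention to treat and is defended by a condition it does not meet. This follows from the text and needs no assumption beyond reading every session as including the first two.

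That the result will be biased does not follow. Dependence of continuation on allocation is a risk that the article's own account of feedback makes credible. Bias is zero if the same rule retains equal shares in both arms. Otherwise its size and direction cannot be determined, because neither the proportion continuing nor its split by arm is given. The shifts above, 0.037 to 0.129 GSI points when the shares are unequal, are illustrations under assumed retention and correlation. The correction still matters, because it changes what the trial may claim.

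**What to change.** 1. **Relabel and limit.** Replace the intention-to-treat statement with modified intention to treat (patients continuing after two sessions), and confine the conclusion to that set. In the Randomisation section, replace the claim of assurance with a statement that comparing baseline characteristics cannot exclude selection bias. Cost: wording only.
2. **Report continuation.** Give the number and proportion continuing past two sessions by arm, with reasons, and a confidence interval for the difference between arms. State who takes the decision and whether non-return counts. Cost: a short table, if disposition is recorded for everyone randomised. Similar proportions and reasons would be reassuring, though not proof.
3. **Add an all-randomised sensitivity analysis of week-12 GSI.** Use baseline data for non-continuers, with delta-shift scenarios for their unobserved outcomes. The delta shifts are essential: imputation or weighting from baseline data alone would share the weakness of the baseline comparison. Check first that non-continuers have a baseline BSI; it is scheduled at first contact, but the list of characteristics for all patients does not name it.

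Item 3 is a sensitivity analysis and not a repair. It is model-dependent, and because only a limited group is expected to continue, much of the outcome would be imputed. It also has less power. As an illustration, let a share f continue, so that 180/f are randomised to obtain 180 continuers. If non-continuers have no effect and the SD is 0.80, the difference becomes 0.3f and one-sided power is:

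| f (assumed) | Randomised | Difference | Power |
|---|---|---|---|
| 0.3 | 600 | 0.09 | 39% |
| 0.5 | 360 | 0.15 | 55% |
| 0.7 | 258 | 0.21 | 68% |

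These powers treat every outcome as observed; imputation would lower them further.
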